## Abstract

**Background:**

HIV testing uptake remains low among men in sub-Saharan Africa. HIV self-testing (HIVST) at the workplace is a novel approach to increase the availability of, and access to, testing among men. However, both access and linkage to posttest services remain a challenge.

**Objective:**

The aim of this protocol is to describe a cluster randomized trial (CRT)—Workplace-Based HIV Self-testing Among Men (WISe-Men)—to evaluate the effect of HIVST in workplace settings on the uptake of HIV testing services (HTS) and linkage to treatment and prevention services among men employed in private security services in Uganda.

**Methods:**

This is a two-arm CRT involving men employed in private security services in two Ugandan districts. The participants in the intervention clusters will undergo workplace-based HIVST using OraQuick test kits. Those in the control clusters will receive routine HTS at their work premises. In addition to HTS, participants in both the intervention and control arms will undergo other tests and assessments, which include blood pressure assessment, blood glucose and BMI measurement, and rapid diagnostic testing for syphilis. The primary outcome is the uptake of HIV testing. The secondary outcomes include HIV status reporting, linkage into HIV care and confirmatory testing following HIVST, initiation of antiretroviral therapy following a confirmatory HIV test, the uptake of voluntary medical male circumcision, consistent condom use, and the uptake of pre-exposure prophylaxis by the most at-risk populations.

**Results:**

Participant enrollment commenced in February 2020, and the trial is still recruiting study participants. Follow-up for currently enrolled participants is ongoing. Data collection and analysis is expected to be completed in December 2021.

**Conclusions:**

The WISe-Men trial will provide information regarding whether self-testing at worksites increases the uptake of HIV testing as well as the linkage to care and prevention services at male-dominated workplaces in Uganda. Additionally, the findings will help us propose strategies for improving men’s engagement in HTS and ways to improve linkage to further care following a reactive or nonreactive HIVST result.

**Trial Registration:**

ClinicalTrials.gov NCT04164433; https://clinicaltrials.gov/ct2/show/NCT04164433

**International Registered Report Identifier (IRRID):**

DERR1-10.2196/25099

## Introduction

### Background

Global estimates report that 81% of people living with HIV (PLHIV) knew their HIV status at the end of 2019, and 67% were on antiretroviral therapy (ART) [1]. Over the past several years, there has been a significant decrease in new HIV infections and an increase in the proportion of people accessing ART, with a consequent decline in AIDS-related deaths [2]. The decline in HIV/AIDS-related deaths is attributable, at least in part, to early initiation of HIV care and improved adherence to ART [2]. While numerous efforts and advances in the fight to end the HIV/AIDS epidemic have resulted in substantial gains, the HIV prevalence of 6.3% in Uganda is still quite high [3]. In 2019, there were approximately 1.4 million PLHIV, and approximately 23,000 died of AIDS-related illnesses in Uganda [4].

The failure to reach greater numbers of men with HIV testing and treatment appears to be driving ongoing cycles of HIV transmission in different settings [5]. Not surprisingly, in Uganda, more women (86%) than men (78%) know their HIV status [6]. This may be partly because, unlike women who attend regular maternity and reproductive health services, men do not have similar touch points within the health care system [7]. Furthermore, there are overlooked gender norms and societal beliefs around masculinity and health testing behaviors [8,9] as well as increasing homophobia and transphobia at health facilities [10,11]. When men living with HIV are not diagnosed in a timely fashion, do not start treatment, or fail to remain on treatment, it endangers not only their own health but also the well-being of their families and communities [12]. The current level of new infections in Uganda is still remarkably high, with an estimated 53,000 newly infected people in 2019 [4]. This may be an indication that the country will continue to register high numbers of people with HIV unless innovative measures are put in place to reach and test hard-to-reach populations such as men and youths [13]. Recognizing the importance of closing this gap, various efforts are being directed at developing innovative strategies to increase men’s engagement in HIV prevention and care.

The Joint United Nations Programme on HIV/AIDS (UNAIDS) campaign “Blind spot: Reaching out to men and boys” encourages HIV programs to design campaigns that promote men’s engagement in HIV services [12]. In line with HIV testing, men in different parts of Uganda have expressed concern with getting tested at a health facility because of the long queues, poor attitudes of health workers, fear of being labeled an HIV “victim,” and stigma [14,15]. Additionally, some men have declined an HIV test for fear of imminent death following a positive result, fear that a positive result would stop them from acquiring new sexual partners, fear of a divorce, and a lack of confidentiality for the test results [16-18]. In that regard, the Uganda National HIV Testing Services Policy and Implementation Guidelines [19] proposed that men be targeted at their workplaces, because that is where they spend most of their time. The goal of workplace HIV testing services (HTS) is to increase access to HIV testing by men and women. This approach has demonstrated success in increasing the uptake of HTS at several male-dominated worksites [6].

We propose the use of HIV self-testing (HIVST) to increase the uptake of HTS at the workplace. HIVST overcomes some of the barriers for standard HTS, such as stigma, long lines at health facilities, lack of time to take a test, and the perceived lack of confidentiality of test results [20,21]. During HIVST, an individual collects his or her own oral fluids or blood, performs the test either in private or with someone he or she trusts, and then interprets the results [22]. According to the World Health Organization (WHO), several studies have demonstrated the feasibility and acceptability of HIVST in diverse populations, including men [23]. In a study conducted in South Africa, Van Dyk observed that participants who preferred HIVST were predominantly men [24]. In Malawi, Zambia, and Zimbabwe, Hatzold and colleagues used several HIVST distribution models among men, young people, and index HIV testers [25]. Current trends indicate that HIVST is gaining traction, and many countries have developed policies and guidelines for large-scale implementation [26]. Therefore, this study aims to assess the effectiveness of HIVST in increasing the uptake of HIV testing among wen in work settings in Uganda. However, even as evidence of the high feasibility, acceptability, and accuracy of HIVST continues to accumulate across many delivery models, there is a need for randomized trials to evaluate the outcomes and cost-effectiveness of different HIVST delivery models. More importantly, trials that focus on the linkage to HIV prevention and treatment remain a necessity.

### Objective

We present the protocol for the Workplace-Based HIV Self-testing Among Men (WISe-Men) study, which is a cluster randomized trial (CRT) to assess the effectiveness of workplace-based HIVST in Uganda. The aim of this trial is to evaluate the effect of HIVST in work settings on the uptake of HTS and linkage to further HIV services among men employed in private security services in Uganda.

### Hypothesis

We hypothesize that workplace-based HIVST will increase the proportion of men who take an HIV test, the proportion of men who initiate ART following a positive result, and the proportion of men who are linked to prevention services following a negative result.

## Methods

### Conceptual Model

This trial is guided by the information-motivation-behavioral skills (IMB) model [27]. The model suggests that health-related sensitization, incentives, and behavioral skills are key determinants for health behaviors. It asserts that if individuals are well informed, receive the appropriate motivation, and have the right behavioral skills, they are more likely to initiate and sustain behaviors that lead to positive health outcomes [28,29]. We use a modified version of the IMB model proposed by a study for HIV testing in the emergency department [28,30] (Figure 1).

**Figure 1 figure1:**
[figure not shown]
Conceptual model adapted from the information-motivation-behavioral skills model. HIVST: HIV self-testing; HTS: HIV testing services; PrEP: pre-exposure prophylaxis; VMMC: voluntary medical male circumcision.

### Study Setting

This study will be conducted in two Ugandan districts, namely Kampala, the capital city, which houses headquarters for most companies offering security services in Uganda, and Hoima, an oil and natural gas base that has several security companies. Additionally, the social and relational dynamics created by the work demands of men working in private security services have an influence on their vulnerability to HIV risk. Many of the workers migrate from their homes to work in cities, which places them at high risk of HIV, especially if they remain away from home and/or away from their regular partners for long periods [31].

### Study Participants

Permission will be sought from the management of each company to allow the research team to meet with the employees at the company premises. The team will meet the employees during the morning meeting to introduce the study and provide information leaflets. The team will then return on another agreed-upon day to enroll participants, collect baseline data, and carry out the workplace HIV testing. On each data collection day, all eligible employees will receive an equal opportunity to participate in the study activities. Initially, the men will receive study information as a group, followed by one-on-one eligibility assessment and subsequent recruitment.

### Study Design

This is a two-arm CRT involving men employed in private security companies. Clusters were private security companies employing 50 or more men in two districts in Uganda. This CRT was informed partly by findings from a previous exploratory qualitative study exploring the perceptions and preferences of employers and employees in private security companies regarding workplace-based HIVST and linkage to further services [32]. The study proposed several strategies to optimize linkage to posttest services following workplace-based HIV testing. These strategies included the use of referral and linkage documentation, paid time off from employers to attend health facilities, assurance of the confidentiality of the test results, peer support from PLHIV, health education and sensitization, expanded clinic hours, the reduction of stigma, and the mitigation of any potential harm. Furthermore, both the employers and employees in the security companies proposed the inclusion of further assessments in addition to HIV testing. This approach would allow them to understand their health status and reduce the stigma associated with taking an HIV test more fully. The additional health assessments include measuring blood pressure and blood glucose, assessing BMI, and screening for syphilis. Participation will be discontinued in response to harm or participant request.

### Site Selection and Allocation

Through randomization, Kampala District was allocated to the intervention arm and Hoima District was allocated to the control arm. The clusters in the intervention arm will receive HIVST while those in the control arm will receive standard HTS.

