### Sample Size Determination

Sample size estimation is based on the primary outcome: proportion of men who take an HIV test. The main outcomes were at the participant level. Currently, approximately 55% of males in Uganda have taken an HIV test [34]. We hypothesize a 15% increase in HIV testing in the workplace HIVST group in comparison to the control group. We considered a two-sided α of .05 with a power of 80% to detect a significant change between both groups, a 1:1 allocation ratio between the intervention and control arms, a response rate of 90%, and a design effect of 1.399. We estimate a minimum total sample size of 548 participants, with 274 per arm. The proxy for design effect was picked from the proxy variable “Had taken an HIV test and obtained results in the past year” [35]. 

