### Statistical Analysis

We will use the intention-to-treat principle for all analyses. Participants’ sociodemographic characteristics will be summarized using frequencies and proportions and will be compared across the study arms. We will employ chi-square and Fisher exact tests for categorical variables as well as means and *t* tests or analyses of variance for continuous variables [41]. To avoid unit-of-analysis errors, we shall conduct analyses by allocation unit via hierarchical logistic regression models that compare the outcome between the two arms and account for clustering among the respondents. The analysis will also adjust for individual-level covariates to elicit associations between the outcomes and the covariates. This method of analysis has been selected over other methods of analyzing cluster data to avoid any ecological fallacy [42]. For the primary outcome, we will compare the proportion of participants taking an HIV test between the two arms. Secondary analyses will be conducted to compare the proportion of HIV-positive participants who become linked to care between the two arms as well as the proportion of HIV-negative participants who take up prevention services between the two arms. The statistical analysis will be performed using Stata software (version 14; StataCorp LP). Trial findings will be published following the CONSORT (Consolidated Standards of Reporting Trials) guidelines [43].

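### One district was randomised to each arm, so arm and district cannot be separated, and the 80% power holds only if uptake does not vary between districts

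*Protocol article*

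**What the plan says.** Site Selection and Allocation in the protocol article reports the randomisation: "Through randomization, Kampala District was allocated to the intervention arm and Hoima District was allocated to the control arm". It continues: "The clusters in the intervention arm will receive HIVST while those in the control arm will receive standard HTS". Each company therefore takes the arm of its district, and the article nowhere describes a separate allocation of companies.

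Study Design names a different unit: "Clusters were private security companies employing 50 or more men in two districts in Uganda". Statistical Analysis then says "we shall conduct analyses by allocation unit via hierarchical logistic regression models", with allowance for clustering among respondents and adjustment for individual-level covariates.

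Sample Size Determination starts from "Currently, approximately 55% of males in Uganda have taken an HIV test" and sets the target: "We hypothesize a 15% increase in HIV testing in the workplace HIVST group in comparison to the control group". It adds "We considered a two-sided α of .05 with a power of 80% to detect a significant change between both groups", equal allocation, "a response rate of 90%, and a design effect of 1.399", and arrives at 548 men, 274 per arm. The design effect is borrowed from a survey variable on recent HIV testing. No separate term for district appears.

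Study Setting describes Kampala as the capital, where most security firms have their headquarters, and Hoima as a base for the oil and gas industry.

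**The concern.** Three sections disagree about the unit. Companies are called the clusters, districts were allocated, and the analysis is to follow the allocation unit. If that unit is the district, no such analysis exists with one district per arm. If it is the company, it is not the unit that was allocated.

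The consequence goes beyond labelling. Any difference in uptake between men in the capital and men in the oil district, for reasons unrelated to self-testing, falls entirely into the estimated arm effect. Randomisation balances such differences only over many units, and here it decided a single either-or choice. At stake is whether the primary comparison can be read as a randomised effect of workplace self-testing, and whether its p-value, confidence interval and stated power mean what they say. The linkage outcomes are exposed in the same way, because they depend on local health facilities.

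**Working it through.** **1. Reproduce the stated sample size.** Inputs from Sample Size Determination: control proportion 0.55; 0.70 under the intervention (15 percentage points); two-sided alpha 0.05; power 80%; design effect 1.399; response 90%.

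- Without continuity correction: n = [1.96 × √(2 × 0.625 × 0.375) + 0.842 × √(0.55 × 0.45 + 0.70 × 0.30)]² / 0.15², which rounds up to 163 per arm.
- With continuity correction: 176 per arm.
- 176 × 1.399 / 0.90 = 273.6, so 274 per arm and 548 in total. This matches the article.
- The uncorrected 163 would give 254 per arm. A relative 15% increase (0.55 to 0.6325) would need about 866 to 903 per arm. Neither matches.

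The arithmetic is therefore right under its own assumptions.

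**2. Degrees of freedom at the level allocated.** Two districts less two arm means leaves 2 − 2 = 0 degrees of freedom. The smallest two-sided randomisation p-value is 2 / C(2,1) = 1.0, whatever the number of men. For comparison, four districts per arm would give 2 / C(8,4) = 2/70 = 0.029, and three per arm 2/20 = 0.10. This step needs no assumed figure.

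**3. What the planned model can absorb.** A fixed district effect is collinear with arm, and a random district effect cannot be estimated. A company random effect describes variation between companies within a district, not the gap between Kampala and Hoima. Individual-level covariates remove only the part of that gap that they explain.

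**4. Size of the distortion (illustration).** The between-district SD of uptake is an assumption, because the article gives none.

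- Effective number per arm: 274 × 0.90 / 1.399 = 176.3.
- SE of the difference under no effect: √(2 × 0.55 × 0.45 / 176.3) = 0.053, or 5.3 points.
- SE including district: √(0.053² + 2 × SD²).
- True type I error of a nominal 5% test that omits district: 2 × [1 − Φ(1.96 × 0.053 / SE including district)].
- Power at 55% vs 70% if the district variance were known: Φ(0.15 / √((0.55 × 0.45 + 0.70 × 0.30)/176.3 + 2 × SD²) − 1.96). This is generous, since one district per arm cannot supply that variance.

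| Assumed district SD (points) | SD of the chance gap between two districts, √2 × SD | SE including district | True type I error | Power, variance known |
|---|---|---|---|---|
| 0 | 0 | 5.3 | 5% | 84% |
| 2 | 2.8 | 6.0 | 8.4% | 73% |
| 3 | 4.2 | 6.8 | 12.6% | 62% |
| 5 | 7.1 | 8.8 | 24.0% | 41% |
| 10 | 14.1 | 15.1 | 49.2% | 17% |

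The 84% in the first row is the formula without continuity correction; with the correction it is 80%, as stated in the article.

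**5. Cross-check on the intraclass-correlation scale.** Take the total design effect as 1.399 + (246.6 − 1) × ρ, where 246.6 = 274 × 0.90 and ρ is an assumed between-district correlation. For ρ of 0.001, 0.01 and 0.05, the type I error is 7.1%, 23.8% and 53.1%, the same order as in the table.

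The term 2 × SD² contains no sample size. More men or more companies in the same two districts do not reduce it.

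**The case against.** The strongest reply is that the plan does not propose a test on two district means. The Statistical Analysis sentence goes on to an individual-level hierarchical model, chosen to avoid ecological fallacy, and its clusters are most naturally the companies. This stands: the plan uses a model that can be fitted, but mislabels its unit and omits district variance.

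The districts may also be more alike on this outcome than their descriptions suggest. Both enrol only men never tested or last tested negative more than a year ago, both offer the same extra health checks, and uptake is measured among enrolled men offered a test at work. This too stands. Nothing in the article supports a 10-point SD, and the mild end of the table deserves equal weight. These features may narrow the gap but do not separate arm from district.

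Four stronger readings are tempting, and the article does not support them:

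- **The sample size is miscalculated.** It reproduces exactly.
- **The borrowed design effect excludes district variation.** Its source is not shown, so the sampling levels it reflects cannot be checked. One can say only that no separate district term is given and that no design effect repairs one unit per arm.
- **Any observed effect would be spurious, or the error rate is known to be near one half.** Neither the size nor the direction of the district difference is known.
- **The design can readily be rescued in mid-trial.** Recruitment was still open, but the article does not say that any company remained unopened, still less in both districts.

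**Conclusion.** The point holds and needs correction. One district was randomised to each arm, so the effect of self-testing and the difference between Kampala and Hoima cannot be separated by any analysis of these data alone. This conclusion, with the 0 degrees of freedom, follows from the stated allocation and needs no assumption.

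The 80% power is correctly computed but conditional on zero between-district variance, a condition the article neither states nor supports. How far the planned test departs from 5% depends on an SD that the article does not give. The type I error of about 8% to 49%, for SDs of 2 to 10 points, is a range of illustration and not an estimate. The study can still provide a controlled comparison of two districts. It cannot carry the inferential weight of a cluster-randomised trial with many allocated units.

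**What to change.** - In Study Design, Site Selection and Allocation, Sample Size Determination and Statistical Analysis, name the district as the allocation unit, one per arm, with companies as clusters nested within districts.
- Withdraw the 80% power claim for a cluster-randomised effect, or state that it assumes no between-district variance.
- Report the study as a two-district controlled comparison, adjusted for baseline individual covariates and for company covariates where available. The article does not say that company covariates are collected.
- Add a sensitivity analysis that adds 2 × SD² to the variance of the difference in uptake, for SDs from 2 to 10 points. At the planning SE, the 95% half-width grows from 10.4 points (1.96 × 5.3) to 11.8 at SD 2, 17.3 at SD 5 and 29.6 at SD 10.
- Word the conclusion to match.

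The cost is wording and one sensitivity analysis. The downside is a less favourable design claim.

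Optional, and only if unopened companies remain in both districts: randomise those within district, stratify by district, and take the randomised contrast from those companies alone. Pooling them with companies already opened would confound arm with calendar time. This would need an amendment, kits and trained staff in both districts, and attention to contamination between arms.

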### Eligibility Criteria

Eligible private security companies, each employing at least 50 male personnel, were identified and listed per district. The eligibility criteria for participants are as follows [33]:

Men 18 to 60 years oldEmployed more than 6 months within the security industryMen who have either never taken an HIV test or who tested negative for HIV more than 1 year ago.

